#### **G.4 Prediction models and secondary analyses**

In addition to the ITT analysis the data collected in the EAGeR trial will be utilized to develop prediction models for various endpoints in the gestation and reproductive process. These models will enhance our understanding of these processes and the factors that may affect outcomes. In that, the study will provide important information beyond the evaluation of the effects of LDA.

The prediction models approach is described here only briefly.

##### *Prediction of live birth*

Various prediction models can be built for this binary event considering baseline and follow-up information. Since women were randomized to receive one of two treatments, we will initially develop separate models for the groups based on the intention to treat assignment with the population at risk being the complete study population. We propose a few modeling approaches as an example.

A model to predict the probability of live birth may be developed based on the information collected at the baseline visit such as demographic information, medical history, and time since last spontaneous abortion. Three methods can be used to build such a model: (a) Logistic regression (b) Neural networks (c) Regression trees. While logistic regression is a standard technique, the other two methods will allow us to consider more complicated associations between risk factors and outcome (e.g. interactions and optimal cut-off points) as well as discrete outcomes with several possible categories (e.g. early pregnancy loss, pregnancy complications, birth). These aspects may be especially interesting for the EAGeR trial where a number of sequentially occurring endpoints are evaluated.

Validation methods will be used to compare these approaches whereby the data will be divided randomly into a training (e.g. 2/3 of the data) and validation sets (e.g. 1/3 of the data). The models will be fit using the training set and their predictive ability will be compared on the validation set. ROC (receiving operating characteristic) curves will be used to compare the different models and determine which is to be preferred. The optimal probability threshold for the logistic and neural network models will be chosen using the Youden Index.

In addition to the models using only baseline information there is interest in considering additional clinical and biomarker information gathered during follow-up. In particular, assessing the influence of true exposure to treatment, taking into consideration compliance to assigned treatment and additional aspirin use. Compliance would need to be accounted for either in a cumulative manner (e.g. >80% compliance over time) or by considering lagged variables with compliance being measured over specified time intervals (e.g. trimesters of pregnancy). In contrast to prediction models based on baseline information, such models would be restricted to prediction for subjects who have reached various stages, for example examining the effect of compliance in say the first trimester of pregnancy conditional on completing the first trimester. For these analyses the sample sizes will be lower and models will include covariates. Therefore, specific power analyses will be conducted to assess the power available for testing specific hypotheses of interest.

Other analytic approaches including survival analysis will be applied for secondary endpoints such as time to becoming pregnant or time from hCG detected pregnancy to early pregnancy loss (EPL). Both Cox regression models and neural networks will be considered for covariates adjustment. Finally, for outcomes that may be repeated over time such as symptoms assessed in the safety interview, methods of longitudinal data analysis with repeated measurements will be applied. These include marginal models, both parametric and semiparametric (e.g. generalized estimating equations approach) and random effect models.

One aspect of the study design that will be addressed carefully in the analysis is the subgroup of women who experience an hCG pregnancy loss and return to follow-up with a chance of becoming pregnant again. The rationale for including this group in the primary analysis of live birth is that typically this type of pregnancy loss would not have been detected. However, these women may contribute more than one pregnancy to the analysis (at most two) and up to two losses. These women may be different from other participants in their characteristics or in how aspirin affects them. Therefore sensitivity analysis will be performed to assess the influence of censoring these women at the time of first event on study results.

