## **G. STATISTICAL ANALYSIS**

### **G.1 Overview**

The EAGeR trial is designed as a multi-site randomized double blind clinical trial with two treatment arms: folic acid + aspirin compared to folic acid + placebo. A fixed sample size of 1600 randomized complete subjects is planned. Thus, for planning and statistical power computations we assume that this is the number of subjects who complete the trial and does not include dropouts.

The primary analysis plan is based on an “intention-to-treat” approach comparing the two treatment arms based on the randomized assignment, ignoring later changes in treatment. This analysis is described in Section G.2. The Haifa DCC will perform periodic partial analyses and present interim reports to the DSMB as requested, during Phase II of the trial. It is anticipated that partial analyses will be performed every 6-12 months. The final analysis will be performed upon completion of data collection and editing in Phase III of the trial. Also one full formal interim analysis is planned and the power calculations with considerations for the choice of optimal time for the analysis are given in Section G.3.

In addition to the intention to treat analysis, the Haifa DCC will engage in methodological research with the Project Officer at the NICHD. The focus is on developing statistical methods for clinical prediction models of reproductive outcomes as described in Section G.4, analysis of intermediate endpoints (Section G.5) and evaluating the effect of dropouts and compliance on the study results (Section G.6).

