The following Tables 3 and 4 present results of power calculations for various interim looks plans for the EAGeR trial. These demonstrate the implications of different choices for the number and timing of interim looks. We assume throughout an alpha level of 0.05 and a sample size of 1600 women divided equally to the aspirin and placebo arms of the trial. Previously published studies suggest that for the control group a probability of about 0.70 - 0.80 for live birth given pregnancy ( $P_{preg}$ ) can be expected. Further, the probability of implantation per cycle ( $P_{implant}$ ) was assumed to be constant and in the range between 0.175 and 0.25. Figure 4 shows the probability of live birth (PLB) considering six cycles of menstruation (including both active and passive follow-up):

$$PLB = P_{preg} P_{implant} \sum_{c=1}^6 (1 - P_{implant})^{c-1}$$

**Figure 4.** Probability of live birth versus implantation probability per menstrual cycle

[figure not shown]

Hence a conservative estimate for the live birth rate would be a combination of implantation rate or 17.5% per cycle and a probability of live birth given pregnancy of 70% yielding an estimated value of  $PLB = 0.479$ . The final calculations will be done after the population from which participants are drawn will be identified. A refinement of the calculation can easily incorporate non-fixed probabilities of implantation per cycle

In the following, we consider a range of probabilities for the placebo + folic acid arm of 0.46, 0.48 and 0.50. The effect of the intervention will be measured as the rate ratio (RR) of live birth in the aspirin + folic acid arm compared to placebo + folic acid. We consider effect sizes of 1.15, 1.20 and 1.25. The calculations were preformed using PASS software. Table 3 presents the resulting power for no interim looks and Table 4 shows the power for one or two interim looks for selected outcome probabilities and effect size.

**Table 3.** Power for comparing live birth rates in treatment and placebo groups with no interim looks.

| Live Birth Probability in placebo arm | Live Birth Rate Ratio to be Detected |            |      |
|---------------------------------------|--------------------------------------|------------|------|
|                                       | 1.15                                 | 1.20       | 1.25 |
| 0.46                                  | .77                                  | .96        | .99  |

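### The live-birth prediction models are ranked on one small hold-out third, and no data or resampling is named to estimate how well the chosen model performs

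*Supplement*

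**What the plan says.** The text is in the latest protocol version in the Supplement, section G.4, under the heading on prediction of live birth.

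- **Arms:** "we will initially develop separate models for the groups based on the intention to treat assignment".
- **Split:** "the data will be divided randomly into a training (e.g. 2/3 of the data) and validation sets (e.g. 1/3 of the data". The plan describes one random division, with the fractions given as examples.
- **Candidates:** logistic regression, neural networks and regression trees are fitted on the training part and compared on the validation part.
- **Selection:** ROC "curves will be used to compare the different models and determine which is to be preferred".
- **Cut-off:** "The optimal probability threshold for the logistic and neural network models will be chosen using the Youden Index". The data set used for this step is not stated.

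G.4 names no third test set, cross-validation, bootstrap, optimism correction or confidence interval for the AUC. It describes the approach as brief and the methods as examples.

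**The concern.** The validation part has two jobs. It decides which of three methods wins, and it is the only named source for how well that winner predicts. Once it has been used to choose, its AUC for the winner is the largest of three noisy values and tends to be too high. The set is also small for an arm-specific model, so the ranking is weak, and a third of the women contribute nothing to fitting.

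At stake is the credibility of the reported discrimination, and of any cut-off for live birth, in new women. The aspirin effect on live birth does not depend on these models.

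**Working it through.** **Inputs from the documents.** G.1: "A fixed sample size of 1600 randomized complete subjects is planned", where "this is the number of subjects who complete the trial and does not include dropouts". G.3: "a sample size of 1600 women divided equally to the aspirin and placebo arms of the trial", so 800 per arm, with a planned live-birth rate of 0.48 on placebo and 0.48 × 1.20 = 0.576 on aspirin. "We assume throughout an alpha level of 0.05"; G.2.2 makes the primary test two-sided.

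**Inputs assumed, because the documents give none.** True AUC 0.60 to 0.70. Correlation r between two models' AUCs on the same women 0.5 to 0.9, with 0 as an extreme for the selection bias.

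**Reproducing the plan's figures.** There is no precision figure for the prediction models, so only the sample size and event rates can be checked.
- Live-birth probability: 0.70 × (1 − 0.825⁶) = 0.70 × (1 − 0.3153) = 0.479, as stated.
- Power at 800 per arm, 0.48 against 0.576: (0.096 − 1.96 × 0.02496) / 0.02485 = 1.895, and Φ(1.895) = 0.971. Table 3 gives .97.

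**Size of the sets, one arm.** Training 800 × 2/3 ≈ 533; validation 800 × 1/3 ≈ 267. Validation on placebo: 267 × 0.48 ≈ 128 live births and 139 without. On aspirin: 267 × 0.576 ≈ 154 and 113.

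**Precision of one validation AUC (Hanley-McNeil).** With m events, n non-events, U = A/(2 − A) and V = 2A²/(1 + A):

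SE² = [A(1 − A) + (m − 1)(U − A²) + (n − 1)(V − A²)] / (mn).

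At A = 0.65, m = 128, n = 139: U = 0.4815, V = 0.5121, A² = 0.4225. SE² = (0.2275 + 7.491 + 12.368) / 17792 = 0.001129, so SE = 0.0336 and the 95% half-width is 1.96 × 0.0336 = 0.066.

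| True AUC | Placebo, 267: SE, half-width | Aspirin, 267: SE, half-width | Placebo, 800: SE, half-width |
|---|---|---|---|
| 0.60 | 0.0347, 0.068 | 0.0346, 0.068 | 0.0200, 0.039 |
| 0.65 | 0.0336, 0.066 | 0.0333, 0.065 | 0.0194, 0.038 |
| 0.70 | 0.0321, 0.063 | 0.0315, 0.062 | 0.0185, 0.036 |

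**Difference between two methods on the same 267 women.** SE of the difference = SE × √(2(1 − r)). At A = 0.65 and r = 0.7: 0.0336 × 0.775 = 0.026, half-width 0.051. Over AUC 0.60 to 0.70 the half-width is about 0.03 at r = 0.9 and 0.06 to 0.07 at r = 0.5. The difference detectable with 80% power is about 0.04 (r = 0.9) to 0.10 (r = 0.5).

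**Bias from reporting the best of three equally good methods.** Expected excess = 0.846 × SE × √(1 − r), where 0.846 is the mean of the largest of three standard normals. At A = 0.65 and r = 0.7: 0.846 × 0.0336 × 0.548 = 0.016. The range is about 0.009 (r = 0.9) to 0.029 (r = 0).

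**Youden index, only if the cut-off is also chosen on the validation third.** Simulation with binormal scores, 128 live births and 139 without, 4000 runs, correlation 0.7 between the scores of three equally good models, empirical maximum of sensitivity + specificity − 1:

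| True AUC | True maximum | Single model, apparent | Winner of three, apparent |
|---|---|---|---|
| 0.60 | 0.142 | 0.194 | 0.217 |
| 0.62 | 0.171 | 0.220 | 0.243 |
| 0.65 | 0.215 | 0.260 | 0.285 |
| 0.70 | 0.289 | 0.331 | 0.355 |

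The excess over the true maximum is about 0.04 to 0.05 for a single model and about 0.07 to 0.08 for the selected winner.

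**The case against.** The text is an outline. The fractions are examples, methods *can* be used, and arm-specific models are only the initial step. A hold-out split is a recognised method, and its stated use is to compare approaches. Nothing says that the winner's validation AUC will be published as its performance, or that the cut-off is set on that part. An empirical Youden maximum is inflated, but a normal-theory estimate on the same simulated data showed no inflation (0.171 against 0.171), and the estimator is not specified.

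Much of this stands, and it limits the point:

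- A reader might infer that the split is made within each arm. G.4 does not say so. The sizes hold anyway, because an arm-specific model has about 267 validation women under either way of splitting.
- A reader might infer that the scheme cannot separate the methods at all. It can detect large gaps, roughly 0.04 to 0.10 depending on correlation. The selection bias is largest when the methods are equal and shrinks if one is truly better.
- A reader might infer that these models are a main product of the trial. The objectives in section A do not list them, and G.1 places them in methodological research beside the intention-to-treat analysis.
- A reader might infer that the reported cut-off is bound to fail in new women. That needs a step the plan leaves open.

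What does not fall is the structure. Hold-out comparison and ROC selection are stated as what will be done. Other fractions only trade fitting data for validation data and leave no untouched set.

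**Conclusion.** The point holds as a modest, inexpensive improvement to a secondary analysis. One random split selects among three methods, and G.4 names nothing else to estimate the winner's performance.

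Imprecision is the larger problem: about ±0.06 to 0.07 on an arm-specific validation AUC. At an assumed correlation of 0.7, differences below about 0.05 are within noise (about 0.03 to 0.07 for correlations 0.9 to 0.5). Selection bias is smaller, about 0.01 to 0.03 in AUC. It arises only if the winner's validation AUC is reported as its performance and the methods are about equally good. The Youden excess depends on the cut-off being set empirically on the same third.

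These sizes rest on 800 completers per arm, the planned live-birth rates, and the assumed AUC and correlation. Fewer completers would make the sets smaller. The primary comparison and its power are untouched.

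**What to change.** In G.4, replace the single split with bootstrap optimism correction or repeated nested cross-validation on all women. Put tuning, the choice among the three methods and the Youden cut-off inside the resampling loop. Report the corrected AUC of the whole procedure with a confidence interval.

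Taking the full-sample standard error as an idealised guide, the AUC half-width per arm falls from about 0.06 to 0.07 to about 0.04 (0.036 to 0.039), and all women contribute to the fit.

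The cost is wording, more computing and probably a less favourable reported AUC. No data collection or sample size changes. Two additions are optional: one model on both arms with treatment and its interactions (with 1600 women the half-width is about 0.025 to 0.028), which is a modelling preference, and calibration measures beside the AUC.

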#### *Secondary outcomes for infants' complications*

For these outcomes, expected to be rare, an intention to treat analysis will be performed using Poisson regression methods to compare the overall rate of these (adverse) events in the two treatment groups. Additional analyses will use live-birth as the denominator to calculate rates.

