### **Study Objectives**

The **primary objective** of the study is:

To determine the effect of low-dose aspirin (LDA) in combination with folic acid on the incidence of live births relative to placebo plus folic acid.

**Secondary objectives** will include:

- a* To determine the effect of LDA in combination with folic acid on the incidence of hCG detected pregnancy relative to placebo plus folic acid.
- b* To determine the effect of LDA in combination with folic acid on the incidence of clinically recognized pregnancy (by 6.5 week ultrasound) relative to placebo plus folic acid.
- c* To determine the effect of LDA in combination with folic acid on specific pregnancy outcomes (gestational age, preterm birth, birthweight [small for gestational age], major neonatal complications, length of hospital stay for infant, preeclampsia, and cost) relative to placebo plus folic acid.

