### G2.2 Intention to treat analysis

The primary analysis of the clinical trial will be “intent to treat” (ITT) analysis based on the total cohort of randomized patients. This approach will be applied to the primary endpoint (live birth) as well as designated secondary endpoints. The difference between the incidence rates of live births for the two treatment groups will be examined by a two-sided test based on the standard Z-score (using the normal approximation to the binomial distribution). The common null hypothesis states that the effect of aspirin on the outcome is null compared to the placebo.

The secondary objectives (as described in Section A) with binary endpoints will be analyzed similarly as comparison of proportions. For binary outcomes such as pregnancy, the time to event may be of interest. In this case, survival analysis methods will be applied with the log-rank test for comparison of the two study treatment groups. For continuous outcome such as birthweight either parametric or non-parametric methods will be used as appropriate. If transformations to approximate a normal distribution are feasible, they will be carried out prior to the parametric analysis. The normality of the data will be examined both graphically using Q-Q plots and by formal tests (Wilks- Shapiro test). For data (either on original or transformed scale) assumed to be normally distributed the comparison of the two treatment groups will be carried out by a t-test. Alternatively if a non-parametric test is required, the Wilcoxon-Mann-Whitney test will be used.

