- V. Withdrawal Form – used to report participant's early withdrawal from follow-up or stopping of Study Pills or folic acid
- VI. Unscheduled Contact Form
- VII. Change Form – used to make any changes in participants information that was entered before on one of the questionnaires.
- VIII. Additional Pills/Barcodes Form

Data from each of these unscheduled forms is handled similarly to the visit associated form.

Report of adverse events:

For the EAGeR trial possible adverse events may include spotting or bleeding at anytime during pregnancy, vomiting and other gastrointestinal effects, intrauterine growth restriction, preterm labor, premature preterm rupture of membranes, congenital anomaly, intrauterine fetal death, placental and other birth complications, neonatal death, severe

maternal morbidity requiring hospitalization, and maternal death. It should be noted that these are symptoms that are also generally consistent with pregnancy, therefore may not be unexpected.

If a severe adverse event is identified while the woman is on follow-up, the staff will alert the site PI and complete the CRF within 2 days of becoming aware of the event. The DCC will update the Project Officer and the DSMB to discuss if any action needs to follow, including stopping of Study Pills/folic acid or unblinding to a health care provider.

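### Infant complications: the Poisson comparison of an overall event rate states no counting unit and no allowance for several complications in one infant, so its type I error can exceed 5%

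*Supplement*

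**What the plan says.** The protocol's Section G.4 has a short paragraph on infant complications. It opens "For these outcomes, expected to be rare, an intention to treat analysis will be performed", and the method is to proceed by "using Poisson regression methods to compare the overall rate of these (adverse) events in the two treatment groups". It then adds "Additional analyses will use live-birth as the denominator to calculate rates". That is the whole specification. The complications are not listed, and no counting rule, dispersion term or variance estimator is given.

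The outcome appears in secondary objective c (Section A), which ends "major neonatal complications, length of hospital stay for infant, preeclampsia, and cost) relative to placebo plus folic acid". Section G.2.1 pairs major neonatal complications with death as one item, to be taken from hospital records and charts. Neither section itemises the complications.

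Two other provisions bear on the point. Section G2.2 sends binary secondary endpoints to a comparison of proportions. Earlier in G.4, GEE and random-effect models are named, but for outcomes repeated over time, such as symptoms from the safety interview. They are not extended to infant complications.

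**The concern.** A Poisson model sets the variance of a count equal to its mean. That is reasonable when each affected infant contributes one event. When one very sick infant contributes several, the counts are over-dispersed and the model-based standard error is too small. Rarity does not cure this: if few infants are affected but each has several events, the counts are still over-dispersed.

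The text leans towards an event count. It speaks of outcomes in the plural and of an overall rate of events, and a single yes/no endpoint would already fall under the proportions rule in G2.2.

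The protocol also gives reason to expect clustering. Section C.4 recognises preterm birth that is indicated because of preeclampsia or a small fetus, and Section B.5 says such conditions often lead to iatrogenic preterm delivery. The general adverse-event list in Section H.3 names overlapping events of one pregnancy, among them "intrauterine growth restriction, preterm labor, premature preterm rupture of membranes, congenital anomaly, intrauterine fetal death".

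At stake is the planned comparison between arms for neonatal harm or benefit. With few affected infants, the chance fall of two or three very sick ones into one arm could produce a nominally significant rate ratio with too narrow an interval.

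**Working it through.** **The plan's own figure.** None is stated for this analysis: no rate, event count, alpha or power. The related live-birth figure reproduces: 0.70 × (1 − 0.825⁶) = 0.479. This gives 0.479 × 800 = 383 live births per arm under placebo, rounded here to 400 for the live-birth denominator.

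**Inputs from the protocol.**
- Section G.3: "We assume throughout an alpha level of 0.05 and a sample size of 1600 women divided equally to the aspirin and placebo arms", so 800 women per arm.
- Section G2.2: a "two-sided test based on the standard Z-score (using the normal approximation to the binomial distribution".

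Both are stated for the primary endpoint. They are borrowed here because nothing is given for infant complications.

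**Assumed inputs (not in the documents).**
- Share of women or live births with an affected infant, p: 2%, 5% or 10%.
- Distribution of K, the number of events per affected infant: as in the table.

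**Formula.** With total counts Y₁ and Y₀ in equal arms, the Poisson Wald statistic is z = log(Y₁/Y₀) / √(1/Y₁ + 1/Y₀). If the true variance is φ times the mean, z has variance of about φ under no effect, so

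type I error ≈ 2[1 − Φ(1.96/√φ)].

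This gives 5.0% at φ = 1.0, 7.4% at 1.2, 16.6% at 2.0 and 25.8% at 3.0.

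The count per woman has mean pE[K] and variance pE[K²] − (pE[K])², so

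φ = E[K²]/E[K] − pE[K].

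**Worked case.** Suppose 80% of affected infants have one event and 20% have two, with p = 0.05. Then E[K] = 1.2, E[K²] = 0.8 + 0.2 × 4 = 1.6, and φ = 1.6/1.2 − 0.05 × 1.2 = 1.27. The type I error is 8.2%.

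**All scenarios.** The simulated column is the range over Wald and likelihood-ratio tests, 100,000 trials per scenario, with 800 per arm at 2%, 5% and 10% affected and 400 per arm at 5% and 10%.

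| Mean events per affected infant | Assumed split (1, 2, 3, … events) | φ at p = 5% | Formula at p = 5% | Simulated range |
|---|---|---|---|---|
| 1.0 | always 1 | 0.95 | 4.4% | 3.7–5.1% |
| 1.2 | 80/20% | 1.27 | 8.2% | 7.3–9.0% |
| 1.4 | 70/20/10% | 1.64 | 12.6% | 11.7–13.5% |
| 1.85 | 50/25/15/10% | 2.31 | 19.7% | 18.8–20.7% |
| 2.3 | 40/20/20/10/10% | 2.97 | 25.6% | 24.5–26.4% |

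**Remedies under the same null.**
- Counting any complication once: plain Poisson rejects 3.6–5.1%. In a separate simulation (40,000 replicates, 800 women per arm, live birth 0.48, 2–10% of infants affected) a two-proportion Z test rejects 4.5–5.2%.
- Counting all events with a woman- or infant-level sandwich variance: 4.8–5.3% (40,000 trials; means 1.2 to 2.3; 800 per arm at 5% and 10% affected, 400 per arm at 10%). The smallest of these cases expects 800 × 0.05 = 40 affected per arm. The 2% case was not run with this estimator, and the negative binomial model was not simulated.

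**The case against.** The strongest reply is that the plan never says each complication enters as a separate event. The sentence is followed at once by the live-birth denominator, so the overall rate could mean the rate over all randomised women, with one yes/no per woman. On that reading plain Poisson rejects about 4–5% and nothing is inflated. The wording also leaves room for a robust or scaled variance. Both points stand as readings. Neither is written down, however, and an analyst following the sentence literally could count all events with software defaults.

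The evidence on clustering also has limits. The list in Section H.3 is a general adverse-event list that includes maternal events, and it does not define infant complications. Preterm birth and small size for gestational age are separate secondary outcomes, and nothing says they are summed in the Poisson model. These places make it plausible that perinatal events cluster, but they do not show how many complications per infant would be counted.

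A reader might go further and infer that the planned test rejects some 14–25% of the time. The documents do not support that. By the formula above it would need φ between 1.76 and 2.90, roughly 1.5 to 2.3 counted events per affected infant, and no section supplies such a figure. Nor do they name this as the analysis for the maternal and fetal safety objective (additional objective d), or say that its interval goes to the DSMB. It belongs to the neonatal part of secondary objective c.

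**Conclusion.** The concern holds conditionally. The paragraph names a method without the two details that decide whether it is valid: the counting unit and the variance estimator. If more than one event per infant is counted and model-based standard errors are used, the test is anti-conservative. One affected infant in five having a second event is enough to reach 7–9%. Over the assumed scenarios the type I error runs from about 4% to about 26%, and the documents cannot place the trial within that range.

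The result rests on a two-sided 5% test, equal arms, and assumed shares affected and events per infant. The events per infant drive it; the share affected matters little. The issue is worth correcting because the method can be wrong on its natural reading and the correction is simple. It concerns a secondary analysis and leaves the primary live-birth test untouched.

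**What to change.** In Section G.4:

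1. Define which events are major infant complications. Make the main comparison the proportion of women (or infants) with at least one, reported as a risk ratio with 95% CI. State the unit for both the all-randomised and the live-birth denominators.
2. If event counts are also analysed, use Poisson regression with robust (sandwich) standard errors clustered on the woman, or a negative binomial model. Do not rely on the model-based Poisson standard error.

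The cost is a sentence or two in the plan and a standard software option, with no new data. The drawbacks are wider intervals for event counts and an any-complication endpoint that ignores how many events each infant had. If very few infants are affected, the sandwich variance is itself less dependable, which is a further reason to let the any-complication comparison lead.
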